### Comparison

Comparison schools will complete the baseline and follow-up data collection but will otherwise continue as usual throughout the academic year 2025–2026. Schools (both comparison and intervention) will be asked to provide usual practice data so the researchers can see whether any new strategies were implemented throughout the year and whether implementing KiVa-SEND changed usual practice in intervention schools.

### Intervention discontinuation or modification

Wherever possible, all participants will remain in the trial for baseline and follow-up data collection. However, any school or individual participant can withdraw from the trial by informing the research team. Modifications to KiVa-SEND can be made where deemed appropriate by the class teacher delivering the materials. In this instance, they should report the modifications on the end-of-lesson teacher report.

### Data collection

#### Pupils

Data collection with the pupils (summer 2025 and summer 2026) will use an adapted version of the Olweus Bully/Victim Questionnaire (OBVQ; [9]). This version includes 20 of the original questions about either being a victim of bullying (10 questions) or bullying others (10 questions). Two new questions have been included which ask whether 1) the pupil has *ever* been bullied and 2) has *ever* bullied another pupil. These questions reflect that often pupils in special schools who have been involved in bullying will struggle to separate the incident with a time restraint, for example, within the past three months. These two additional questions allow the pupils to answer more broadly, before being asked to focus in on a limited time window. Based on previous piloting with pupils from three additional special schools, adapted answer options will also be provided which simplify the original OBVQ answer options. Adapted answer options: 1) ‘this has never happened to me’, 2) ‘this hasn’t happened to me since I started in this year group’, 3) ‘this has happened two or three times since I started in this year group’, 4) ‘this has happened to me lots of times since I started in this year group’, 5) ‘I don’t want to say’. Data has, and will be collected on a 1:1 (researcher:pupil) basis unless the school deems small group data collection possible (1:2 or 1:3). Data collection takes approximately 10 min per pupil and is preferably conducted in a quiet room near the pupil’s classroom, or where necessary, in a quiet area within the pupil’s classroom. In some cases, pupils may have an accompanying adult assigned to support them in school. In these instances, this adult joins them when completing the questionnaire with the researcher. The adult supports these pupils to stay focused and to answer the questions, as they do during usual classroom time, but does not reply on behalf of the pupil and where possible, does not look at which answer the pupils selects. All data collection is via electronic tablets with the researcher reading every question-and-answer option out loud, and where needed, pointing to the accompanying text on the pupil’s screen. Where possible, the pupil makes their selection on the tablet whilst the researcher (and any other pupils or adults) look away. Allowing the child to select an answer on their own provided tablet encourages the child to provide an honest answer. Once an answer has been selected, that question disappears and the next appears.

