### Participant timeline

#### Data analysis

As a feasibility trial, most of our outcome data will be descriptive. Missing data will be reported but no imputation will take place. Data will be summarised at baseline and follow-up by trial arm. Exploratory analysis on primary and secondary outcome measures (OBVQ, TSDQ and TPB) will be conducted between trial arms at the follow-up time point, with the baseline as a covariate, whilst considering school clustering. Although we are not testing the effectiveness of the KiVa-SEND programme during this feasibility trial, we shall explore the pupil and teacher survey data descriptively and statistically, to ensure they are viable options to use in a full trial or whether they do not appear appropriate for this cohort.

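### As printed, the adapted pupil bullying questionnaire has no true answer for a pupil with exactly one event in the current school year

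*Protocol article*

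**What the plan says.** The Protocol article (Data collection – Pupils) describes 20 retained OBVQ items, 10 on being bullied and 10 on bullying others, plus two added questions on whether either has ever happened. Of the added questions it says: "These two additional questions allow the pupils to answer more broadly, before being asked to focus in on a limited time window". The answer options were simplified after piloting in three other special schools. There are five of them:

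- Option 1 denies that the event has occurred at any time in the pupil's life.
- Option 2 limits the denial to the current year: "this hasn’t happened to me since I started in this year group".
- Option 3, the lowest that admits a current-year event, reads "this has happened two or three times since I started in this year group".
- Option 4 stands for many events in the current year, with no number attached.
- Option 5 lets the pupil decline to answer.

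No separate answer set is printed for the bullying-others items, and no scoring rule is given.

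Under Data analysis, the OBVQ is compared between arms at follow-up, "with the baseline as a covariate", as an exploratory analysis allowing for school clustering. Missing data are reported and not imputed. The same section says the survey data will be explored to see whether the measures are viable for a full trial, and Aims makes suitability of the outcome measures the secondary aim.

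**The concern.** A frequency scale should give every respondent one true answer. This one steps from no event this year to two or three, so a pupil bullied once has nowhere to go. The error falls on the boundary between none and any, and on the boundary between one event and repeated events. A definitive trial would be likely to report prevalence at one or both.

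The quantitative checks in this study are poorly placed to find the problem. Table 2 counts pupil data collected, and Feasibility outcomes relies on returned questionnaires plus researcher feedback. A pupil who picks a false option still counts as a completed return. Where possible the researcher looks away during selection, and the question then disappears from the screen. Field notes on comprehension, or the process evaluation, might pick it up if a pupil speaks up, but nothing directs them to it. The measure could therefore be judged suitable and carried into the full trial with the gap still in it.

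**Working it through.** The article states no figure on this point, so there is none to reproduce. The check has two parts.

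**1. Which options are literally true for each history?** Inputs are the five printed options. Option 4 has no number attached and is read as four or more, which is an assumption; no sensible reading of it covers one event. Option 5 carries no frequency.

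| Events ever | Events this year | True options among 1–4 |
|---|---|---|
| 0 | 0 | 1 and 2 |
| 1 or 3 | 0 | 2 |
| 1 or 3 | **1** | **none** |
| 2 | 2 | 3 |
| 3 | 3 | 3 |
| 4 or 10 | 4 or 10 | 4 |

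Exactly one event this year is the only count tested that has no true option. The separate 'ever' questions do not rescue it. A pupil who has ever been bullied and then chooses option 2 may have been bullied only in earlier years, or once this year and had to deny it.

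**2. How far can prevalence move?** Let P be the true share of pupils with any event this year on an item, and s the share of all pupils with exactly one. The article gives neither at item level, so both are assumed.

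- All one-offs choose option 1 or 2: measured 'any' = P − s, too low by s. 'Two or more' is right.
- All choose option 3 or 4: measured 'any' = P, which is right. 'Two or more' is measured as P instead of P − s, too high by s.
- All choose option 5 and drop out: measured 'any' = (P − s)/(1 − s), too low by s(1 − P)/(1 − s). This is no more than s, because P is at least s.

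The error on either measure is therefore at most s. With the planned 296 pupils (Sample size):

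- s = 5%: 0.05 × 296 = 14.8, about 15 pupils; at most 5 points.
- s = 15%: 0.15 × 296 = 44.4, about 44 pupils; at most 15 points.

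As an illustration, take P at the two ends of the 25–69% bullying range quoted in Background, used here only as stand-ins for an item-level rate, and let 10%, 30% or 50% of those pupils be one-offs:

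| P | One-offs among them | P − s: measured 'any' if all choose option 2; also true 'two or more' |
|---|---|---|
| 25% | 10% / 30% / 50% | 22.5% / 17.5% / 12.5% |
| 69% | 10% / 30% / 50% | 62.1% / 48.3% / 34.5% |

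If all choose option 3 instead, measured 'two or more' is 25% or 69% in every column. The option 5 route with P = 25% and s = 0.30 × 25% = 7.5% gives 0.175/0.925 = 18.9%, a loss of 6.1 points. At P = 69% the higher one-off shares imply s = 20.7% and 34.5%, beyond the 5–15% range. The spread shows how little the article pins down.

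**The case against.** The strongest reply is that this is a feasibility study with no hypotheses. The OBVQ analysis is exploratory, no progression threshold depends on bullying prevalence, and the answer set is the same in both arms. All of that is true, and it limits the consequence. It does not remove the point, because judging the measure is one of the study's aims.

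A second reply is that the options were piloted and simplified for pupils who find time limits hard. The article does not say that single events were left out on purpose. If only repeated events were meant to count, option 2 would still be false for a one-off victim; its wording would have to include a single event.

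Third, the article may not reproduce the whole instrument. The printed options are worded for victims, and nothing is shown for the bullying-others items. This stands: the gap for perpetration is inferred, and the tablet form has to be checked.

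A reader might also infer that having two options that both mean zero this year is itself an error, because a 1–4 score would rank a pupil bullied only in the past above one never bullied. The article does not support that. It states no such score, and the two options separate lifetime from current-year experience for each item. A never-involved pupil can truthfully pick either, which is harmless if both count as zero for the current year.

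Nor is it right that one-off pupils are always forced into a wrong frequency. Option 5 is a way out, though it loses the answer.

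**Conclusion.** The concern holds in a limited form. On the printed wording the answer set is not exhaustive: a pupil with exactly one event in the current year group must choose a zero option, an option of two or more, or the refusal. Current-year 'any' and 'repeated' prevalence are therefore misclassified by an amount the article does not allow one to estimate. The bound of 5–15 points rests on an assumed 5–15% of one-off pupils on an item, and on all of them moving the same way.

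The conclusion also assumes that the tablet form matches the printed list. For bullying others it is an inference. A reader might go further and conclude that the between-arm comparison is biased. Nothing in the article shows a differential effect, since both arms use the same form. The point is worth acting on because the measure is a candidate for the definitive trial, but it does not threaten the progression criteria.

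**What to change.** First confirm that the printed list matches the tablet form, including the options used for the bullying-others items. If it does, the next step depends on timing. Follow-up is set for April to July 2026 and the article is dated 11 April 2026, so it may already be under way.

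- **If follow-up has not begun:** add an option for one event since starting the year group, in both arms and on the paper back-ups. Analyse follow-up with that category merged first with option 2 and then with option 3. State plainly that the two codings show sensitivity at follow-up only. Pupils with one event at baseline could have picked any of the five options, and their answers cannot be recovered.
- **If follow-up has begun in any school:** keep the form unchanged in all schools and report that none and any this year cannot be cleanly separated.

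In either case, state how a single event is answered and coded, and count options 1 and 2 both as zero in any current-year score. Report the missing category as a finding on the measure's suitability, and carry an exhaustive answer set into the definitive trial.

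The cost is a form edit, one extra coding and a few sentences of reporting. The drawbacks of a change at follow-up are that the new option is unpiloted and that the instrument then differs from baseline. Because the planned comparison is between arms at follow-up with baseline only as a covariate, the same change in both arms does not bias it.

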
#### Staff

Data collection with teachers of the selected pupils will involve completing two questionnaires in the summer of 2025 and in the summer of 2026: 1) the Teacher Strengths and Difficulties Questionnaire (TSDQ; [6]), a 25-item behavioural screening questionnaire and, 2) an adapted version of the Teachers’ Perception on Bullying questionnaire (TPB [14],), adapted to be answered specifically for each individual pupil. It involves six questions about the pupil being a victim of bullying and six questions about the pupil engaging in bullying others. Questions will be answered using a 5-point Likert scale from ‘hasn’t happened’ to ‘several times a week’, with an extra option to select ‘unsure’. Questionnaires will be printed out on paper and given to the teachers in class packs (one questionnaire per pupil participating). Data collection will take approximately 2 min per pupil questionnaire set, but teachers will have 2–3 days to complete the questionnaires. Teachers assigned to the KiVa-SEND arm of the trial will deliver the 20 KiVa-SEND lessons and for each lesson will note pupil absenteeism. They will also complete a short check sheet on material covered in that lesson (adherence) and suitability of the content (feasibility).

#### School

Data will be collected electronically via secure transfer, from all eight schools. The following data will be provided for every participating pupil: age, sex, class, teacher, primary educational need (using the English school census 13 SEND options) and whether they have a learning disability (moderate, severe, profound and multiple). The schools will also electronically provide their current bullying and behaviour policies and will answer questions on their current anti-bullying programmes.

#### Researchers

Field notes will be collected on paper during data collection in summer 2025 and summer 2026 and transferred to an electronic notes file. Notes will include whether data was collected 1:1 or in a small group (two to three pupils), where data was collected (in the classroom or in a private space), whether an accompanying adult was present (and their level of involvement), level of pupil comprehension (none, limited, good), whether any adaptations had to be made to the questionnaire (such as text size increase or use of symbols), time taken, and another note of relevance.

#### Process evaluation

After two terms (end of spring 2026), in person or remote interviews will be carried out with three to six members of staff (semi-structured interviews of approximately 20 min each). In person conversations will also be carried out with up to 10 pupils (semi-structured interviews or Talking Mats for approximately 10 min each). The split will be one to two teachers from one to two usual practice schools and two to four teachers from two to four interventions schools and all pupils will be from intervention schools. The process evaluation will assess 1) recruitment and retention, 2) implementation and adherence of the adapted KiVa-SEND programme, 3) enjoyment, engagement and acceptability of/to pupils and staff, 4) suitability of the outcome measures (Table 1).

**Table 1 Tab1:** Schedule of enrolment, data collection, and intervention

	Study period				
	Enrolment	Baseline	Allocation	Intervention phase	12-month follow-up
Timepoint	0	*t*^1^	*t*^2^	*t*^3^	*t*^4^
Eligibility	X				
School opt-in	X				
Parents opt-out	X				
Pupil assent		X			X
Allocation			X		
Pupil demographics		X			
KiVa-SEND				X	
Pupil Olweus Bully/Victim Questionnaire		X			X
Staff Teacher Strengths and Difficulties Questionnaire		X			X
Staff teachers’ perception on bullying		X			X
Teacher reporting				X	
Process evaluation				X	
Lesson fidelity				X	
Pupil attendance				X	

### Participant timeline

#### Data analysis

As a feasibility trial, most of our outcome data will be descriptive. Missing data will be reported but no imputation will take place. Data will be summarised at baseline and follow-up by trial arm. Exploratory analysis on primary and secondary outcome measures (OBVQ, TSDQ and TPB) will be conducted between trial arms at the follow-up time point, with the baseline as a covariate, whilst considering school clustering. Although we are not testing the effectiveness of the KiVa-SEND programme during this feasibility trial, we shall explore the pupil and teacher survey data descriptively and statistically, to ensure they are viable options to use in a full trial or whether they do not appear appropriate for this cohort.

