Some mainstream school-based anti-bullying interventions have been found to reduce school-level victimisation by, on average, 15–20% with some findings of up to 50% [5]. Programmes such as KiVa [11], a Finnish anti-bullying programme for pupils aged 7–15, are used in mainstream schools, are evidence-based and show effectiveness in reducing victimisation and increasing empathy in UK primary schools [4]. Any pupil can be involved in bullying, yet certain risk factors increase the likelihood of becoming perpetrators and/or victims of bullying. Combined bullying data from two large studies of children and young people from 144 countries found that the greatest risk factor to becoming a victim of bullying was being ‘different’ to one’s peers. These differences included factors such as physical appearance, physical or learning disability, nationality and family-level disadvantage [15, 16]. It is therefore essential to ensure that any resources and programmes used with the most vulnerable pupils such as those with SEND, are appropriate and effective.

The current trial is in response to the lack of understanding and research into anti-bullying programmes for pupils with SEND, a particularly vulnerable population when it comes to bullying involvement. There is a clear lack of evidence-based support, and the need for an RCT to evaluate a potentially suitable intervention. Recently, a preliminary adaptation of two KiVa lessons for use with special school populations was deemed successful with regards to engagement, acceptability and feasibility [2]. The full adaptation is now complete and known as KiVa-SEND.

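### Ruling out all imputation while adjusting for baseline discards pupils who have a follow-up score but no baseline score, at an avoidable cost in precision

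*Protocol article*

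**What the plan says.** The Data analysis section of the protocol article fixes two things. On missing data: "Missing data will be reported but no imputation will take place". On the model: "Exploratory analysis on primary and secondary outcome measures (OBVQ, TSDQ and TPB) will be conducted between trial arms" at follow-up, "with the baseline as a covariate, whilst considering school clustering". The first rule makes no exception for baseline covariates. The section also limits the aim: "Although we are not testing the effectiveness of the KiVa-SEND programme during this feasibility trial".

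Four other places bear on who can lack a baseline score:

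- Under Study setting, pupils assent on the day of data collection; Table 1 lists assent at both baseline and follow-up.
- The exclusion criteria remove pupils who joined after baseline, so late joiners are not the issue.
- A footnote to Table 2 counts a pupil as recruited unless a parent or guardian opted the pupil out. Baseline data collected is a separate row of that table.
- Table 2 rates pupil baseline collection green from 80% and amber from 60%. For teacher baseline data the limits are 90% and 70%.

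**The concern.** A model with baseline on the right-hand side needs a baseline value for every pupil in it. If none may be filled in, a pupil without one leaves the analysis, even with a complete follow-up questionnaire. The definitions above allow such pupils: they are recruited, were absent or did not assent on the first occasion, and took part on the second.

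What is at stake is precision. The trial has eight schools, and the arm estimates for the Olweus Bully/Victim Questionnaire (OBVQ), the Teacher Strengths and Difficulties Questionnaire (TSDQ) and the Teachers' Perception on Bullying questionnaire (TPB) will be imprecise in any case. Discarding follow-up scores already collected makes them more so, with no gain in return.

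**Working it through.** **The plan's own figure.** The Sample size section gives 296 pupils and 75% retention with a 95% interval of 70% to 80%. Check: 1.96 × √(0.75 × 0.25 / 296) = 0.049, so 70.1% to 79.9%. It reproduces. It concerns retention only; the article gives no standard deviation, intraclass correlation (ICC) or precision target for the arm comparison.

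**Pupils lost.** Take 296 as recruited pupils, 75% with follow-up, and missingness at the two visits as independent (an assumption). Then 296 × 0.75 = 222 have a follow-up score.

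- Baseline completion 80%: 222 × 0.20 ≈ 44 dropped, 178 analysed.
- Baseline completion 60%: 222 × 0.40 ≈ 89 dropped, 133 analysed.
- Teacher measures at their limits, holding 222 for comparison: 222 × 0.10 ≈ 22 and 222 × 0.30 ≈ 67 dropped.

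**Effect on the standard error.** Assumed: total variance 1, baseline to follow-up correlation r = 0.5, ICC 0.01 or 0.05, four equal schools per arm, school variance not reduced by adjustment. Per school, let m_c be the pupils with both scores and m_d those with follow-up only.

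- Complete-case variance of a school mean: V_cc = ICC + (1 − ICC)(1 − r²)/m_c
- All follow-up scores kept: V_all = ICC + 1 / [m_c/((1 − ICC)(1 − r²)) + m_d/(1 − ICC)]
- SE of the arm difference: √(2V/4) = √(V/2)

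Example at 80% and ICC 0.01, with m_c = 178/8 ≈ 22.2 and m_d = 44/8 ≈ 5.55:

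- V_cc = 0.01 + 0.7425/22.2 = 0.0434, SE 0.147.
- V_all = 0.01 + 1/(22.2/0.7425 + 5.55/0.99) = 0.01 + 1/35.5 = 0.0382, SE 0.138.
- The fall is 6.3%.

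| Baseline complete | ICC | SE, complete-case | SE, all follow-up | Fall |
|---|---|---|---|---|
| 80% | 0.01 | 0.147 | 0.138 | 6.3% |
| 80% | 0.05 | 0.203 | 0.196 | 3.1% |
| 60% | 0.01 | 0.165 | 0.141 | 14.7% |
| 60% | 0.05 | 0.215 | 0.198 | 8.0% |

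Simulations of this layout, using a baseline mean plus missing indicator, gave falls of 3.0% to 6.6% at 80%. At 60% they gave 6.4% to 15.9%; the 6.4% came from one run at ICC 0.05. At the teacher limits the same formulas give 1.4% to 2.9% (90%) and 5.3% to 10.2% (70%).

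**Bias.** In a further simulation (8 schools of 37 pupils, r = 0.5, ICC 0.05), baseline missingness was made to depend on the baseline bullying score. The complete-case arm difference was off by −0.002 SD with no true effect and by 0.001 SD with a true effect of −0.3 SD. With a simulation error of 0.002, that is no detectable bias. The design explains why: the Blinding section says schools learned their allocation after their baseline data were collected.

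**The case against.** The case for leaving the text alone is fair in several respects. Reporting missing data without imputing is usual in a feasibility trial. The comparison is exploratory, the article generates no hypotheses, and no row of Table 2 depends on the adjusted model. The descriptive summaries by arm and time point do not need complete pairs. The 80% and 60% figures are progression limits, not expected rates. The Sample size section also calls 296 the baseline sample size. If that means pupils with baseline data, all 222 retained pupils have a baseline, and the counts of 44 and 89 do not arise from that total. Against this, 296 is 37 classes of 8, which looks like a class-roll count; the text leaves it open. All of this keeps the point small. It does not remove it, because the two rules as written still drop any pupil with follow-up only.

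A reader might infer more than the article supports:

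- **One unanswered item voids a scale.** The OBVQ offers "I don’t want to say" and the TPB comes "with an extra option to select ‘unsure", so item non-response will occur. But the article states no all-items rule and does not forbid prorating. Scoring of part-completed scales is commonly left to the statistical analysis plan, which is not shown.
- **The rule biases the scores.** Refusal linked to bullying is plausible, but the article gives no refusal data. Refusal that depends on bullying at follow-up could lower the mean scores, and could bias the comparison, chiefly if it differs by arm. That would be missing not at random: the sentence on imputation does not cause it, and standard imputation would not cure it.
- **Standard deviations are inflated.** Fewer pupils widen standard errors, not standard deviations.
- **The adjusted model decides whether the measures are viable.** Pupil completion is judged by returned questionnaires and researcher feedback, and suitability by process evaluation and field notes.

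**Conclusion.** The point holds as a minor one. Read together, the two rules make an ordinary adjusted model complete-case on the pair of scores, and recruited pupils with follow-up only are discarded. For the pupil measure the avoidable loss is about 44 of 222 follow-up scores at 80% baseline completion and 89 at 60%. Recovering them lowers the standard error by roughly 3–6% and 8–16%. For the teacher measures the loss is smaller, because their completion limits are higher. The arm difference is less precise but not biased by this.

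These sizes rest on independent missingness at the two visits, 296 as a count of recruited pupils, a correlation of 0.5 and an ICC between 0.01 and 0.05. None of the four is settled by the article.

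**What to change.** In the Data analysis section, restrict the rule to outcomes and say who is analysed, for example: *Missing follow-up scores will not be imputed. Every pupil with a follow-up score will be included in the comparison of arms.* Then name one of two methods:

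- Model baseline and follow-up jointly, with a common baseline mean across arms and school clustering. This uses pupils with one score and involves no imputation.
- Keep baseline as a covariate, set a missing baseline to the overall baseline mean, and add a missing indicator. This is a simple fill-in of a covariate, so the text must allow it.

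Report the complete-case result as a sensitivity analysis. It would also help to say whether 296 counts recruited pupils or pupils with baseline data.

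The cost is a few words and slightly more analysis work, with no new data. The joint model relies on scores being missing at random, and the complete-case analysis beside it shows how far the result depends on the choice of method.
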